#### Qualitative data analysis

Content qualitative analysis will be employed. Summative content analysis involving counting and comparisons of keywords or content followed by the interpretation of the underlying context will be conducted. Atlas Ti ® software will be used to assist in coding and locating particular words or phrases from the transcribed interviews and discussions. A deductive coding frame to extract code frequencies will be developed. The data will be analyzed for emerging key themes and the findings will be interpreted based on the research questions. Quotes will also be extracted for each of the themes that emerge from the data.

### Cost analysis

The study will utilize the concept and methodology used in Zambia regarding retention in care and outpatient costs for children on ART [28]. We will estimate the total annual costs of fixed costs and use an appropriate measure to allocate them on a pro-rata basis. This will be achieved by recording the number of patients that visit the study facilities (apart from HIV patients) during the study period, that will enable fair allocation of fixed costs per patient. This will be done for all shared resources within the facility. Buildings and equipment costs will be estimated using a replacement approach and annualized. The annual cost will be divided by the total number of active patients in that year for each facility. The administrative cost contribution per patient will be calculated by dividing the annual salaries for administrative staff by the number of active patients for each year for each facility.

Total costs for each arm will be disaggregated into two, namely (1) total costs including start-up costs to capture costs that would have been introduced by the study and (2) costs excluding start-up costs to capture routine cost of care.

A cost outcomes analysis will be conducted from a provider perspective for each arm at 12 and 24 months. The total cost for each arm will be calculated as the sum of the fixed and variable unit costs, and the average cost per patient per year for each arm will be calculated. The average cost per patient retained in care and average cost per patient virally suppressed will be calculated at 12 months and 24 months.

The patient-level cost analysis will involve comparing the baseline average patient costs with patient costs reported at 12 and 24 months for each arm, and comparing costs between arms. The analysis will consider number of visits made to the facility and lost potential production time.

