The aim of this study is to compare the clinical effectiveness and cost-effectiveness of three models of ART provision for stable ART patients in Zimbabwe, with medication pick-ups extended up to 6 months. The objectives are to measure patient retention, virological suppression, acceptability and provider and patient costs amongst stable patients who receive ART at 3- and 6-monthly intervals within CARGs. These groups will be compared to standard of care, facility-based, 3-monthly ART delivery.

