### Outcomes and hypotheses

The rationale for the control arm selection is that provision of ART refills 3-monthly at the facility is the most established standard of care option for stable ART patients in Zimbabwe. All outcomes will be compared between all three arms. The primary outcome is participant retention in care, defined as the proportion of participants remaining in care 12 months after enrollment by intention-to-treat. Retention in HIV care is one of the most important determinants of the overall impact of ART [21]. Retention in care will also be compared after 24 months.

The principal hypotheses are that participant retention in both the intervention arms will be non-inferior to retention in the control arm with a non-inferiority margin of − 3.25% (risk difference). An additional hypothesis is that retention in intervention arm 6MC will be non-inferior to retention in intervention arm 3MC. The rationale for the non-inferiority design is that we anticipate retention to be at least similar in the intervention arms vs. control, and anticipate that provider (and participant-level) costs will be lower in the intervention arms vs. the control due to reduced participant contact with healthcare facilities in the intervention arms. If clinical outcomes in the intervention arms are at least non-inferior compared to the control arm, the interventions are anticipated to show cost savings compared to the control.

The secondary outcomes are:I.The proportion of participants achieving virological suppression 12 and 24 months after study enrollmentII.The proportion of participants retained in the study model of care after 12 and 24 monthsIII.Average annual cost per participant from a provider perspectiveIV.Average provider cost per participant retained, and average provider cost per participant retained with virological suppression 12 and 24 months after enrollmentV.Average annual participant-level expenditure to access treatmentVI. Qualitative research to assess the acceptability of multimonth dispensing (MMD) of ART within CARGs from both a participant and healthcare provider perspectiveVII. Site-level indicators of potential facility-level decongestion during the study. These are:Median difference in facility patient waiting times after 12 and 24 months compared to baselineTrend in the monthly number of patients newly initiated on ARTTrend in the monthly number of patients who receive provider-initiated HIV counseling and testing at the clinic

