### Sample size estimation

Participant sample size estimates were calculated for the primary outcome of retention in care 12 months after enrollment. Sample size estimates were determined for a non-inferiority test for the difference in two proportions in a cluster-randomized design, using PASS® v.14 software. Participant enrollment numbers are assumed to be equal at each cluster. The probability of participant retention 12 months after study enrollment in the control group is assumed to be 95%, derived from the relative difference in reported retention between 12 and 24 months of ART in Zimbabwe [17]. The probability of retention in the intervention arms after 12 months is also assumed to be 95%. An intracluster correlation coefficient of 0.01 for retention amongst stable ART patients associated with the same healthcare facility is assumed [26]. The non-inferiority margin is prespecified as − 3.25% (risk difference). Assuming *α* = 0.05, power of 85%, and using the one-sided Z-test (unpooled) statistic, 192 participants will be required to be enrolled per facility, with 1920 participants per arm and a total sample size of 5760 enrolled participants. As retention in care is the primary outcome, no adjustment for LTFU is made. Assuming that 75% of those on ART at a healthcare facility will be stable [17] and that 60% of these will consent to be enrolled, to reach the required sample size per facility, selected facilities require at least 430 adults currently receiving ART.

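### The aim is to compare cost-effectiveness, but the only measures joining provider cost to outcome are average ratios within each arm, which can favour a cheaper arm with retention below the non-inferiority limit

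*Protocol article*

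**What the plan says.** The title names cost-effectiveness, and the Background section states: "The aim of this study is to compare the clinical effectiveness and cost-effectiveness of three models of ART provision".

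The Cost analysis section gives the method. "A cost outcomes analysis will be conducted from a provider perspective for each arm at 12 and 24 months", and then "The average cost per patient retained in care and average cost per patient virally suppressed will be calculated at 12 months and 24 months". Item IV of the secondary outcomes (Outcomes and hypotheses) lists averages of the same kind.

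Three other statements bear on the point:

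- Outcomes and hypotheses says "All outcomes will be compared between all three arms". Mean provider cost (item III), the averages in item IV and retention are all among those outcomes.
- The same section says that, if clinical outcomes are at least non-inferior, "the interventions are anticipated to show cost savings compared to the control".
- The Data analysis plan gives a cluster-adjusted risk difference for retention with a 95% confidence interval. The Cost analysis section says that patient-level costs will be compared between arms.

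Nowhere does the article join a difference in provider cost to a difference in outcome, or describe their joint uncertainty.

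**The concern.** A comparison of cost-effectiveness asks what is gained or given up in outcome for the change in cost when one model replaces another. One average ratio per arm does not answer that. It divides all spending by all successes, so a fall in cost can outweigh a fall in retention without either difference being shown.

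The article expects provider costs to be lower in the intervention arms, so a cheaper arm with uncertain retention is the case the analysis must handle. The results are meant to inform health policy. A reader of the economic results could take the lowest cost per retained participant as the most cost-effective model, even if that arm had missed the trial's own retention limit.

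**Working it through.** **Inputs from Sample size estimation.**

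- Control retention: "The probability of participant retention 12 months after study enrollment in the control group is assumed to be 95" per cent.
- Intervention retention: "The probability of retention in the intervention arms after 12 months is also assumed to be 95" per cent.
- Margin: "The non-inferiority margin is prespecified as" −3.25% (risk difference).
- ICC 0.01, with 10 facilities of 192 (1920 participants) per arm, one-sided alpha 0.05 and stated power 85%.

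The article gives no provider costs. Control cost is therefore set at 100 units per participant (assumption), and the saving is varied.

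**Plan's own figure.** No cost or cost-effectiveness figure is stated, so the only design figure to reproduce is the power.

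- Design effect = 1 + 191 × 0.01 = 2.91.
- SE of the risk difference = √(2 × 0.95 × 0.05 × 2.91 / 1920) = 0.0120.
- Power = Φ(0.0325/0.0120 − 1.645) = 85.6%, against 85% stated.

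The same variance inputs are used below.

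**When the average ratio favours the cheaper arm.** Write C for mean cost and R for retention, with subscripts I (intervention) and C (control). The intervention ratio is lower when C_I/R_I < C_C/R_C, that is, when the relative saving exceeds 1 − R_I/R_C. The approximate 95% interval for the risk difference is (R_I − 0.95) ± 1.96 × √{[0.95 × 0.05 + R_I(1 − R_I)] × 2.91/1920}.

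| Intervention retention | Saving needed for the better ratio | Approx. 95% CI for the difference (points) | Fewer retained per 1920 |
|---|---|---|---|
| 91.75% | 3.4% | −5.9 to −0.6 | 62 |
| 90% | 5.3% | −7.8 to −2.2 | 96 |
| 87.75% | 7.6% | −10.3 to −4.2 | 139 |
| 85% | 10.5% | −13.2 to −6.8 | 192 |

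The first two rows fail non-inferiority, but their intervals straddle −3.25. The last two lie wholly below it.

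**What the ratio leaves out.**

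- Retention 90%, cost 90: average ratios are 100/0.95 = 105.3 and 90/0.90 = 100.0, so the intervention looks better. The differences are 10 units saved and 5 points of retention lost, or 10/0.05 = 200 saved per retained participant lost.
- Retention 87.75%, cost 92: 92/0.8775 = 104.8, still below 105.3. Here 8/0.0725 = 110 is saved per retained participant lost.

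**The value judgement hidden in the comparison.** The condition C_I/R_I < C_C/R_C can be rewritten as C_I − C_C < λ(R_I − R_C), with λ = C_C/R_C. Comparing average ratios is therefore the same as computing net benefit with a retained participant valued at the control arm's average cost of retaining one, here 105.3 units. The article neither states nor justifies that value.

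**Why an incremental ratio should not lead.** The design assumes equal retention, so the expected effect difference is 0, with an approximate 95% interval of ±1.96 × 0.0120 = ±2.35 points. With an assumed saving of 10 units, the ratio is 10/0.0235 ≈ 425 in size at either end, with opposite signs, and is undefined at zero.

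**The case against.** The strongest reply is that the article does not misuse these ratios.

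- A reader might infer that cost-effectiveness will be judged by the ratios and that the lowest one wins. The article says only that they will be calculated. It states no ranking rule and does not let a ratio override the retention result.
- A reader might also infer that no between-arm comparison of cost and effect is planned, or that a loss of retention would be hidden. That goes too far. All outcomes are to be compared between arms, so the cost and retention differences both fall within the plan. A failure of non-inferiority would be reported as the primary result, and the stated rationale ties expected savings to non-inferior outcomes.
- An arm at 91% might be called clearly inferior. At 91% against 95%, the approximate interval is −6.7 to −1.3 points. It excludes zero but straddles the margin, so that label does not fit.
- The article condenses a fuller protocol and draws its costing method from a cited study that is not at hand. Details of incremental and uncertainty methods may sit elsewhere, and the savings used here are assumed.

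Most of this stands and limits the point. What remains is that the article does state how provider cost is joined to outcome, and that measure does not answer the stated aim. Comparing the item IV averages between arms is itself the comparison that can mislead. The link between savings and non-inferiority is a rationale, not a rule for reading the ratios.

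**Conclusion.** The point holds in limited form. The stated measure joining provider cost to outcome does not by itself deliver the promised comparison of cost-effectiveness. If compared between arms, it favours an arm at the non-inferiority limit once that arm is more than 3.4% cheaper. It favours an arm wholly below the limit (87.75% retention) once that arm is about 8% cheaper.

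These thresholds rest on 95% control retention, ICC 0.01, 1920 per arm and a normal approximation without the planned small-sample correction. Whether savings of that size will occur is unknown from the article. The ratios are secondary outcomes, so the primary conclusion on retention is unaffected. It would be too strong to say that the cost-effectiveness aim cannot be met, since both component differences fall within the plan. This is a cheap improvement, not a flaw in the design.

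**What to change.** In the Cost analysis section, for 3MC vs 3MF, 6MC vs 3MF and 6MC vs 3MC:

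1. Report the difference in mean provider cost beside the difference in retention, and beside the difference in suppression. Give 95% intervals that respect facility clustering and the randomisation strata.
2. Summarise cost and effect jointly on the cost-effect plane, or as incremental net benefit, λ × (difference in retention) − (difference in cost), over a stated range of λ, the value per retained participant. Do not lead with an incremental ratio, which is unstable when the retention difference is near zero.
3. Interpret a cost difference alone as a saving only where non-inferiority has been shown.
4. Keep the average costs per retained and per suppressed participant as descriptive results.

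The costs and outcomes needed are already being collected, so recruitment and data collection do not change. The cost is analyst time and the need to choose and state a range of values per retained participant, which the article does not supply.

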### Site-level data analysis

Summary measures of patient waiting time for each facility at each assessment point will be calculated. The difference in waiting time at 12 and 24 months vs. the baseline survey will be calculated within each arm, and differences in waiting time will be compared between arms. In addition, between-arm comparisons of 12- and 24-month waiting times will be conducted with a two-level, mixed-effects linear model including the median baseline facility waiting time as a fixed covariate and specifying facility as a random effect. A secondary analysis will involve inclusion of other site-specific potential confounding variables as fixed effects in the model.

Plots will be drawn of the monthly numbers of patients newly initiated on ART and monthly numbers who receive provider-initiated HIV counseling and testing per site for each arm to assess trends during the study period, and multilevel, mixed-effects linear regression will be used to compare arms. A secondary analysis will include adjustment for potential site-specific confounding.

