### Recruitment and enrollment procedures

Figure 2 illustrates the overview of time schedules for enrollment, interventions and assessments according to SPIRIT. During the enrollment period, study nurses will screen all patients arriving for ART-refill visits at the study facilities and patients in recently formed CARGs according to the eligibility criteria. Potentially eligible patients will be invited by the study nurses to participate in the study, and to receive viral-load testing. It is not mandatory for all patients in a CARG to participate in the study. Eligible patients at each site who provide informed consent and who have a viral load < 1000 copies/ml will be enrolled until the facility enrollment cap has been reached. All study participants at a particular facility will receive the same model of care based on the arm to which that facility has been allocated. Patients already in CARGs at facilities in the control arm at the commencement of the study will not be considered for recruitment, and they will continue to receive care in CARGs as per the national guidelines similar to those in the 3MC arm.

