### Participant follow-up

All participants will be followed up for 24 months. As retention in care is the primary outcome, there will be no involvement regarding defaulter tracking beyond which exists routinely at each facility. Viral-load testing will occur at annual intervals, according to national guidelines [18]. Participants who become pregnant, develop tuberculosis or other opportunistic infections, have unsuppressed viral loads (≥1000 copies/ml), or who become clinically unwell will require clinic follow-up visits more frequently than 3-monthly as per national guidelines, thus they will transition off the study arm. These participants will remain under observational follow-up for the remainder of the study period for ascertainment of the primary outcome. CARG participants will return to be followed up at the facility. Frequency of ART-dispensing and clinical management will then be determined based on clinician assessment and national guidelines.

As Zimbabwe is moving to have ART refills provided in CARGs as an additional option for stable ART patients at all facilities [18], participants in the 3MF arm will be consigned to receive ART 3-monthly supplied at the facility for 12 months after enrollment; thereafter, participants will be offered the option of forming CARGs that receive ART 3-monthly. Participants who decline to join CARGs will continue to be followed up as arm 3MF for a further 12 months. This design was chosen taking into account program implementation plans for PEPFAR partners as they prioritize the roll-out of CARGs. It will allow arm 3MF to have at least 12 months of follow-up time to analyze retention and virologic suppression. After 24 months, all participants will receive nationally applied standard of care as at the time of study completion.

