## Discussion

No large-scale trials have been conducted investigating patient-level outcomes and health system costs of extended ART-dispensing intervals for patients within community-based groups in sub-Saharan Africa. The rationale for this study is to provide evidence regarding the effectiveness and cost-effectiveness of extended dispensing intervals for ART patients within CARGs, and whether these are suitable strategies that can be implemented on a larger scale to help overburdened health facilities with the large numbers of patients and reduce the burden and cost to patients of frequent clinic visits. Study results are expected to inform health policy both in Zimbabwe and in the entire sub-Saharan African region.

The trial is implemented through a collaboration between Kheth’Impilo AIDS Free Living, EQUIP Innovation for Health, the Organization for Public Health Interventions and Development, FHI 360, the Zimbabwe AIDS Prevention Project Trust and the Zimbabwe MOHCC. Implementation challenges include large distances between facilities, limited access to routine viral-load testing within the country and limited Internet connectivity in rural areas.

The strengths of the study include that a variety of outcome data will be analyzed including clinical effectiveness data, provider- and patient-cost data, qualitative data and site-level impact data. Routine ART facilities from both urban and rural areas are included in a pragmatic design, which is expected to allow study results to be generalizable to other sub-Saharan African settings. The study limitations include that participants in the 3MF arm may not complete 24 months’ follow-up in this arm as, according to MOHCC operational recommendations, they will be provided the option of forming CARGs after 12 months of study participation. The sample size in the 3MF arm may thus be reduced at the 24 months’ outcomes assessment, thus comparisons may have reduced power. However, this will not impact the primary outcome ascertainment of patient retention 12 months after enrollment. Participant viral-loads results may not be complete due to limitations in the availability of viral-load testing in the country. Viral suppression is thus a secondary outcome. It will also not be possible for participants or providers to be blinded as to the study group allocation.

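### Monthly ART initiations and HIV testing are compared between arms over the whole study period, although 3MF participants may join 3-monthly CARGs after month 12, which dilutes the contrast with 3MF

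*Protocol article*

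**What the plan says.** All statements are in the protocol article.

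- **Comparator.** The aim at the end of Background says of the CARG groups: "These groups will be compared to standard of care, facility-based, 3-monthly ART delivery".
- **Outcomes.** Secondary outcome VII in Outcomes and hypotheses is headed "Site-level indicators of potential facility-level decongestion during the study". Two of its three indicators are trends in monthly facility counts: new ART initiations and provider-initiated HIV testing. Waiting time, the third, has separate 12- and 24-month points; the two monthly series have none.
- **Analysis.** Site-level data analysis plots the monthly numbers per site "to assess trends during the study period, and multilevel, mixed-effects linear regression will be used to compare arms". A secondary analysis adjusts for site-specific confounding.
- **Duration.** Participant follow-up states: "All participants will be followed up for 24 months".
- **Control arm after month 12.** The same section holds 3MF participants to facility dispensing for 12 months and continues: "thereafter, participants will be offered the option of forming CARGs that receive ART 3-monthly". The move is optional: "Participants who decline to join CARGs will continue to be followed up as arm 3MF for a further 12 months".
- **Acknowledged limitation.** The Discussion mentions this only as a matter of numbers and power: "The sample size in the 3MF arm may thus be reduced at the 24 months".

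**The concern.** The two series cover two control regimes, and only the first is the comparator named in the aim. After month 12, a facility analysed as 3MF may have part of its enrolled participants in the model that defines 3MC.

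For participant-level outcomes, a 12-month analysis avoids this. For a facility's monthly total there is no participant to exclude, because the facility itself is the unit and its exposure changes. The consequence is bias toward no difference, which the Discussion's remark about sample size and power does not cover.

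With waiting time, these series are the trial's quantitative evidence on whether CARG dispensing frees facility capacity. If it does, the comparison as written understates by how much.

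**Working it through.** The plan gives no effect size, power or uptake for these outcomes, so there is no figure of its own to reproduce. Its sample size concerns retention and does not bear on this point.

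**Inputs.** From the article: 24 months of follow-up; CARG offer to 3MF participants after month 12; 192 participants per facility; CARGs of 6–12; the collection schedules in Description of interventions; recruitment from 28 July to about the end of December 2017 (about 5 months). Assumed: uptake u of 30%, 60% or 100%; CARG size 9 (mid-range); effect on the counts proportional to the share of participants moved.

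**1. Facility refill visits per year, as a proxy for load**

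- 3MF: 192 × 4 = 768
- 3MC: 192 + 3 × 192/9 = 256
- 6MC: 192 + 192/9 ≈ 213

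The control in year 2 has (1 − u) × 768 + u × 256 visits. The contrasts are:

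| | Year 1 | Year 2, u = 30% | 60% | 100% |
|---|---|---|---|---|
| 3MF − 3MC | 512 | 358 | 205 | 0 |
| 3MF − 6MC | 555 | 401 | 247 | 43 |

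The interval difference keeps the 6MC contrast above zero at full uptake, but on visits only by about 43 of 555.

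**2. Mean contrast over months 1–24, 3MC vs 3MF, immediate effect**

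Set the full effect to 1. Intervention is 1 throughout; control is 0 in months 1–12 and u in months 13–24. The mean contrast is 1 − u/2 = **0.85, 0.70, 0.50**.

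**3. The same with a 5-month linear build-up after each start**

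The build-up shortfall sums to 0.8 + 0.6 + 0.4 + 0.2 = 2.0 months.

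- Intervention mean: (24 − 2)/24 = 0.917
- Control mean: u × (12 − 2)/24 = 0.417u
- Contrast: 0.79, 0.67, 0.50, which is 86%, 73%, 55% of the 0.917 expected without uptake

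**4. Slope difference, if one straight line per arm is fitted to months 1–24**

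Sxx = 24 × (24² − 1)/12 = 1150.

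- Immediate effect: intervention slope 0. Control Sxy = 72u, so its slope is 12 × 72u/1150 = 0.75u per year. Intervention minus control is −0.23, −0.45, −0.75 of the full effect per year.
- 5-month build-up: intervention Sxy = 21, control Sxy = 69u. The difference is 12 × (21 − 69u)/1150 = 0.00, −0.21, −0.50 per year (+0.22 with no uptake). It is negative only above u = 21/69 ≈ 30%.

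Uptake above which the slope difference turns negative, by build-up time:

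| Build-up (months) | 0 | 3 | 6 | 9 | 12 | 15 or more |
|---|---|---|---|---|---|---|
| Threshold | 0% | 16% | 38% | 60% | 88% | never |

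If 12 pre-study months are included in the fit, the slope difference is not negative for build-ups of 0, 6, 12 or 24 months. It falls to zero only for an immediate effect with full uptake.

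**5. Restricting to months 1–12**

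The mean contrast is 1.00 (immediate), 0.83 (5-month build-up: 10/12), 0.79 (6-month) or 0.54 (12-month), whatever the uptake. For an immediate effect the months 1–12 slope difference is zero although the level contrast is 1. A post-start slope alone is therefore not enough: levels adjusted for pre-study counts, or pre-study months in the model, are needed.

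**The case against.** **The analysis plan may settle it.** This is a condensed article, and time terms and analysis windows are often left to the statistical analysis plan. That is fair for the model's form. The window, however, is stated here as the study period, with no division at month 12.

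**Control facilities do not convert.** A reader might infer that every 3MF facility becomes a 3MC facility at month 12. The article does not say so: enrolled participants are offered an option, and those who decline stay in 3MF. The dilution depends on an unknown uptake and could be small.

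**Sign reversal is not established.** A reader might infer that the analysis would show control facilities improving faster. Outcome VII is called a trend, but the analysis section states no arm-by-time slope and does not exclude pre-study months. Reversal needs a straight line fitted to post-start months, an effect that builds within about 12 months, and enough uptake. Five months of recruitment make an instant effect unrealistic, and nothing in the article says how fast freed capacity turns into initiations or tests.

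**CARGs already running at control facilities.** For patients already in CARGs there, the article says "they will continue to receive care in CARGs as per the national guidelines similar to those in the 3MC arm". A reader might count this as part of the same fault. It is a baseline feature of unstated size and produces no shift at month 12.

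**Other evidence would show the problem.** Monthly plots could reveal a change at month 12, waiting time is compared separately at 12 months, and qualitative work addresses decongestion. This limits the harm but does not correct the regression estimate.

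**Conclusion.** The point holds as a dilution of the 3MF contrast in the two monthly series. Given a real effect, any uptake above zero biases the full-period comparison with 3MF toward no difference. With an immediate effect proportional to uptake, the 24-month mean contrast of 3MC with 3MF keeps 85%, 70% or 50% of the effect at 30%, 60% or 100% uptake. With a 5-month build-up it keeps 86%, 73% or 55% of its value without uptake. Loss for 6MC vs 3MF is somewhat less, because the dispensing interval still differs. 6MC vs 3MC is not affected by the offer.

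Uptake, speed of effect and proportionality are assumptions; the article gives none of them. Reversal of a slope difference is a conditional possibility and not a property of the stated analysis. The outcomes are secondary, and retention at 12 months is untouched. The change is worth making because it is cheap and the acknowledged limitation does not cover the bias.

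**What to change.** In Site-level data analysis, for monthly ART initiations and HIV testing:

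1. Make the main comparison of 3MC and 6MC with 3MF use the months before CARGs are first offered to study participants at control facilities, with the same window in all arms. Alternatively, fit the whole series with a change point at that date.
2. Adjust for each facility's pre-study monthly counts from the same routine records. With 10 facilities per arm, ranging from rural clinics to hospitals, unadjusted levels would mostly reflect facility size.
3. Report later months separately, labelled as a comparison with a control that has been offered CARGs.
4. Report CARG uptake at each control facility.
5. Keep the full period for 6MC vs 3MC.

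**Cost.** This is analysis wording, plus pre-study months from records already to be used and a count of control participants joining CARGs. The price is fewer months in the 3MF contrast. The offer comes 12 months after each participant's own enrolment, so a facility that enrols over 5 months has only about 12 − 5 = 7 months between its last enrolment and its first offer. If the effect builds slowly, the early window shows only part of it (a mean of 0.54 of the full effect with a 12-month build-up). In that case the change-point version is the better choice.
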